The aims of the present study are twofold: to describe the protocol for both (1) the cross-sectional study to refine the hypotheses and (2) a Randomized Controlled Trial (RCT) to compare the preliminary effectiveness and feasibility of the Mindfulness-Based Health Promotion (MBHP) and Attachment-Based Compassion Therapy (ABCT) programs regarding the usual care on the eating behavior of patients with progressive weight gain after bariatric surgery. It was hypothesized that both interventions are feasible and effective to improve eating behavior, but the compassion-based program is superior to the mindfulness-based program because it addresses specific psychological skills (such as self-compassion) that mediate the effects on eating behavior and well-being.

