#### Outcomes

The primary outcome will be a change in the eating behavior (TFEQ-21, Rep (eat)-Q, and BES) at all steps. Secondary outcomes will be improved quality of life (M-A QoLQII), increased satisfaction with body image and reduced distortion (BSSA), better weight management (maintenance or weight reduction), increased frequency of physical activity, and monitoring with the surgery team. The explicative variables will be the level of mindfulness (MAAS), self-compassion (SCS-SF), anxiety (HADS), and attachment style (ECR-R).

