#### Assessment

Quantitative and qualitative assessments will be performed before the intervention (T0), immediately after the intervention (T1) and at the six months follow-up (T2). Participants will respond to the same electronic form used in Phase 1 of the study at the three evaluation moments (T0, T1 and T2) and after the intervention they will be able to respond subjectively about their adherence to the sessions, frequency of performing formal practices and report if there were unexpected effects (adverse events) in periods T1 and T2 by completing another electronic form [46]. After six months of follow-up, the control group will be offered the intervention (MBHP or ABCT) considered most effective to improve eating behavior (Fig. 2).

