#### Analyses plan

Descriptive statistics will be used to determine the feasibility, acceptability, and effect of Mindfulness-based and compassion-based interventions. The initial baseline characteristics will be revised visually for an approximate balance between groups. For the sociodemographic questionnaire (including the different surgical procedures performed), absolute and relative frequencies will be calculated for categorical variables, whereas means and standard deviations will be estimated for continuous variables.

Statistical procedures will be performed on an intention-to-treat and/or per-protocol basis. For data tabulation and analysis, Excel 2010 programs and SPSS software version 23.0 for Windows (SPSS Inc.; Chicago, IL, USA) will be used. All variables will be subjected to the Kolmogorov-Smirnov test to verify the normal distribution of data. For initial comparisons between the groups, the unpaired *t*-test (two-tailed) or Mann-Whitney U test (two-tailed) will be used for continuous variables whereas Fisher's exact test (two-tailed) and the chi-square test will be used for categorical variables.

After the intervention, a within- and between-group comparative analysis of the scales will be performed with initial and final data using the paired and unpaired *t*-test (two-tailed) for variables with normal distribution (mean, standard deviation, and 95 *%* confidence interval) and the Mann-Whitney U test (two-tailed) for variables with non-normal distribution. Differences between the initial and final means (Δ) of the study variables will be calculated and a comparative analysis of these means will be performed using the *t*-test for independent samples or the Mann-Whitney U test. Statistical procedures will be performed per protocol based on the intention-to-treat analysis. The number needed to treat (NNT) and the number needed to harm (NNH) will be calculated.

To identify the correlation between the study variables and HADS scales, the MAAS, SCS, MAQoLQII, Rep(eat)-Q, TFEQ-R21, BES, ECR-R-Brazil, silhouette scales, and Pearson's and Spearman's correlation coefficient will be used at three time points. At the end of the study, linear regression analyses will be performed with the total sample using complete cases and stratified by weight gain to assess the mediating effect of the statistical relationship between the study scales in the intervention group.

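### The planned mediation regressions relate one scale to another, with no arm-to-mediator path and no order in time, so they cannot show that a programme acts on eating through self-compassion

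*Protocol article*

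**What the plan says.** The Introduction gives the reason for expecting Attachment-Based Compassion Therapy (ABCT) to do better than Mindfulness-Based Health Promotion (MBHP): "it addresses specific psychological skills (such as self-compassion) that mediate the effects on eating behavior and well-being". This is a directional claim: programme, then self-compassion, then eating.

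Under Outcomes, the candidate mechanisms are listed: "The explicative variables will be the level of mindfulness (MAAS), self-compassion (SCS-SF), anxiety (HADS), and attachment style (ECR-R"). The outcome of the path is eating behaviour: "The primary outcome will be a change in the eating behavior (TFEQ-21, Rep (eat)-Q, and BES) at all steps". Under Assessment, data are collected "before the intervention (T0), immediately after the intervention (T1) and at the six months follow-up (T2"), and "Participants will respond to the same electronic form used in Phase 1 of the study at the three evaluation moments", so mechanism and outcome scales are completed together.

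Two sentences of the Analyses plan deal with relations between scales. One is about association: Pearson's and Spearman's "correlation coefficient will be used at three time points". The other is the only one that mentions mediation. It says that at the end of the study "linear regression analyses will be performed with the total sample using complete cases and stratified by weight gain", and that their purpose is "to assess the mediating effect of the statistical relationship between the study scales in the intervention group".

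**The concern.** The hypothesis needs two links: randomised programme to self-compassion, and self-compassion to eating. The mediation sentence describes neither as a path. Its object is the relationship between scales, which is an association and has no direction. It names no arm term, no baseline value and no rule that the mediator is measured before the outcome.

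It also says both that the total sample is used and that the effect is assessed in the intervention group. The two must be reconciled, because they decide whether any treatment contrast exists. Within one intervention arm, allocation is constant, and nothing estimated there can be the part of a treatment effect that passes through a mediator. If both active arms were meant, a contrast between them would be possible, but none is named.

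At stake is the mechanism claim, which is the protocol's stated reason for expecting ABCT to be superior. Scales that are merely related could be reported as evidence of mediation.

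**Working it through.** **Sample sizes used.** The Sample size section gives 43 evaluable per group. For 30% versus 5%, two-sided 5% and 80% power, the two-proportion formula gives 36 without and 43 with continuity correction, so 43 reproduces. The stated 54 is 43 × 1.25 = 53.75, rounded up. A 25% loss from 54 leaves 54 × 0.75 = 40.5, so I also use 40.

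**Why the regression has no direction.** In a simple regression of standardised scales, the slope of eating on self-compassion equals r, and so does the slope of self-compassion on eating. Both have t = r√((n−2)/(1−r²)). With r = 0.5 and n = 43, t = 0.5 × √(41/0.75) = 3.70 either way round.

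**Simulation A: two opposite truths.** There are two arms of 43 and 4,000 runs, with scales coded so that higher is better. Assumed, not in the documents: arm effect 0.5 SD on the driving scale; path 0.5 from the driving to the driven scale at T1; carry-over from T1 to T2 of 0.3 to 0.5.

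| Quantity | Self-compassion drives eating | Eating drives self-compassion |
|---|---|---|
| T1 correlation | 0.51 | 0.51 |
| T1 slope within one intervention arm | 0.50 | 0.50 |
| That slope significant | 94.3% | 94.6% |
| T1 product of coefficients, two arms | 0.25 | 0.13 |
| T2 eating on T1 self-compassion and arm, no T1 eating | 0.50 | 0.25 (significant in 70%) |
| Same, adjusted for T1 eating | 0.30 (significant in 85%) | 0.00 (significant in 6%) |

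The product of coefficients follows by hand. In the forward case it is 0.5 × 0.5 = 0.25. In the reverse case the arm shifts self-compassion by 0.5 × 0.5 = 0.25, and 0.25 × 0.5 = 0.125 appears as an indirect effect that does not exist. With 54 per arm the within-arm slope is significant in about 98% under both truths. The last row becomes 91% and 5%, and the row above it still gives 80% under the reverse truth. A time lag alone is therefore not enough; the earlier eating score must be in the model.

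**Simulation B: error rate and power of a full mediation test.** The driving scale has T1 = 0.5 × T0 + arm effect + noise and T2 = 0.7 × T1 + noise. The driven scale is b times the driving scale plus noise at each visit. Assumed: b = 0.3 or 0.5; arm effect 0.5 or 0.8 SD; 40 per arm. Mediation is declared when arm-to-mediator and mediator-to-outcome are both significant.

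- Plain scale-on-scale regression: significant in about 79–100% of trials with two arms pooled and 46–92% within one arm, equally often under either truth.
- Joint test without time order, reverse truth only: falsely significant in about 6–41%.
- T1 mediator, T2 outcome, adjusted for T0 mediator and T0 and T1 outcome, reverse truth: falsely significant in about 0.3–3%.
- Same time-ordered model when mediation is real: power about 26–65%. The T1/T1 baseline-adjusted model has about 47–97%.

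The 85% in simulation A and the 26–65% here answer different questions. The former tests one slope where T1 self-compassion has its own direct effect on T2 eating. The latter tests both links, where that effect reaches T2 eating only through later self-compassion.

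**The case against.** A reader might infer that the plan fixes same-visit regressions. It does not. The words about the end of the study date the analysis; they do not say which visit supplies predictor or outcome. Elsewhere the section computes initial-to-final differences, so baseline values are in use. This is a journal article, and the visit, lag and covariates of a secondary model are commonly left to a fuller plan. That stands: silence on those details is not the fault.

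A reader might also take the correlations at three visits as the mediation test. They are a separate sentence with their own descriptive aim. That stands too.

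The claim that almost any data would support mediation goes too far. The 79–100% is only a scale-to-scale slope. A proper joint test is falsely significant in about 6–41%, and only under a reverse-only truth with assumed effects.

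A time-ordered replacement has a real price. Adjusting for T1 eating removes mediation already complete at eight weeks, when the training takes place. If residual eating scores correlate 0.5 between visits, power falls to 5–13%.

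Finally, the trial seeks preliminary evidence, and ABCT against MBHP is judged by between-group comparisons, not by this regression. That limits the weight of the point. It does not remove it, because the mediation sentence is not silent: it states a method and a population, and both are unsuited to the hypothesis. A fuller plan would have to replace it, not add to it.

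**Conclusion.** The point holds in limited form. As worded, the mediation analysis is a regression of scale on scale, set both in the total sample and in the intervention group. It names no arm-to-mediator path, no mediator-before-outcome order and no baseline adjustment. Such a regression cannot support the directional hypothesis: under the assumed effects it is significant in about 94% of runs with 43 in the arm, whichever scale drives the other. Within one intervention arm it has no treatment contrast at all.

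The documents do not support saying that the regressions are same-visit, that the correlations are the mediation test, or that mediation would be found in almost any data.

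The lack of direction in the regression is algebraic and needs no assumption. The percentages rest on effect sizes, paths and carry-over that the documents do not give. The primary comparison is unaffected. The sentence should be changed because the mechanism claim depends on it.

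**What to change.** Replace the mediation sentence with a model across the randomised arms. The mediator is SCS-SF (and, separately, MAAS) and the outcome is the eating score. Arm is in both equations, T0 mediator and T0 outcome are covariates, and the indirect effect is given with a bootstrap 95% confidence interval. State one analysis population, so that the total sample and the intervention group no longer conflict.

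Report two versions side by side:

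- **Time-ordered:** mediator at T1, outcome at T2, adjusted also for the T1 outcome. This is the one that addresses direction.
- **T1/T1, baseline-adjusted:** more power, but it cannot exclude the reverse path.

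Label same-visit correlations and same-visit regressions as descriptive, and any mediation result as exploratory.

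The cost is wording only, since all three visits are already planned. The limits should be stated with the result. The time-ordered version has about 26–65% power under the assumed effects with 40 per arm, partly misses mediation completed within the eight weeks, and loses participants who drop out before T2. Neither version removes confounding between mediator and outcome, because self-compassion itself is not randomised.

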#### Research ethics approval

This study was approved by the Research Ethics Committee from the local Institutional Review Board, under the CAAE protocol reference number 18529519.5.0000.5505, in August 2019. Participants will sign the Informed Consent Form online and data confidentiality will be guaranteed.

## Discussion

To the best of our knowledge, this RCT is the first to directly compare the effectiveness of a protocol of CBI (ABCT) with an MBI (MBHP) in bariatric patients with progressive weight regain in feeding behaviors settings. Both programs in this study were developed to meet the cultural characteristics of Latin Americans [19,45] with maximum feasibility, safety and efficacy.

The present study is made relevant given the possible consequences for both physical and emotional health in the progressive weight regain [4,10], especially since training in the MBHP and ABCT protocols may increase levels of mindfulness, self-compassion and reduce levels of anxiety, as observed in other studies [18,21], and also promote improvements in quality of life, satisfaction with body image and reduced distortion. Thus, it is believed that the reduction of negative emotions or better management skills of these emotions can improve eating behaviors, mainly with the reduction in the prevalence of grazing, binge eating, cognitive restriction, emotional eating and uncontrolled eating, all of which were previously associated with weight regain and increased psychological distress [8,11,[14], [15], [16]].

Well-being improvement can mobilize better self-care engagement, for instance increasing the frequency for both monitoring with the surgery team and physical activity. Together, all the previously mentioned aspects can contribute, in medium to long term, to a better weight management (maintenance or weight reduction) throughout life.

And finally, it was hypothesized that ABCT training could be more effective than the mindfulness program because it has lots of ‘constructive’ practices and this family of practices may aim to promote healthy interpersonal dynamics, to strengthen a commitment to ethical values, or to nurture habits of perception that lead to enhanced well-being [20]. Also, because attachment orientation may be a factor worth considering when addressing disinhibited eating, especially in the context of poor outcomes following bariatric surgery [48]. If this hypothesis is confirmed, further studies will be needed to confirm whether this can be considered another strategy with potential for adjuvant treatment of post-bariatric obesity recurrence.

This study will, however, have data collection limitations since it will be conducted with a self-administered online questionnaire, which does not allow participants to discuss any questions that arise during its completion or to compare results with face-to-face interventions, besides any memory bias when reporting high and retrospective weight.

## Conclusion

This study seeks to gather preliminary evidence on the effectiveness of mindfulness and compassion training for the adjunctive treatment of progressive weight gain in post-bariatric patients.

## Data Availability

No data was used for the research described in the article. No data was used for the research described in the article.
